**Feasibility measurement data**	
Feasibility	Recruitment rates, reasons for ineligibility or refusal
Practicability	Proportion of usable video gait recordings, participant adherence to accelerometry, proportion of missing data, questionnaire completion rate, technical performance, sensitivity of measurements to detect change and unexpected problems during assessments or interventions
Acceptance	Retention rate, drop-out rate
**Clinical measurement data**	
Video-based gait analysis	Spatiotemporal parameters (eg, gait speed, stride length and cadence)
	Kinematic parameters (eg, joint angle trajectories in sagittal plane (hip, knee, ankle))
Accelerometry	Duration of physical activity/resting periods
	Intensity of physical activity
Haemophilia Joint Health Score (HJHS)	Range of motion in elbow, knee and ankle on both sides
	Extent of swelling in elbow, knee and ankle on both sides
	Muscle atrophy
	Crepitation in elbow, knee and ankle on both sides
	Flexion deficit in elbow, knee and ankle on both sides
	Extension deficit in elbow, knee and ankle on both sides
	Joint pain in elbow, knee and ankle on both sides
	Muscle strength
	Global gait (walking, stairs, running, hopping on one leg)
**Medical record data**	
Disease specific parameters	Disease severity
	Factor activity
	Traumas
	Therapy
	Quantity of factor administrations
	Secondary diagnoses
	Medical history and injuries, bleeding events
	Clinical, laboratory chemistry and imaging findings (as far as collected during routine care)
**Patient-reported outcome measures**	
Activity questionnaire (MoMo-AFB)	General and personal data
	Physical activity in general
	Physical activity in age-specific settings
	Physical activity in everyday life
	Physical-sports activity in clubs
	Physical-sports activity in leisure time outside club
	Social support
	Enjoyment of physical activity
	Physical self-concept
	Physical activity environment
Health-related quality of life (EQ5DY5L, adults: EQ5D5L)	Agility/mobility
	Self-care
	General activities (eg, work, study, housework, family and leisure activities)
	Pain/physical discomfort
	Anxiety/dejection
	Current state of health on a visual analogue scale (VAS) between 0 and 100
HEP-Test-Q (haemophilia patients only)	Physical condition
	Mobility
	Strength and coordination
	Endurance
	Body perception
Haemo-QoL (haemophilia patients only)	Physical health
	Feelings
	Self-perception
	Sports and leisure
	Work and school
	Dealing with haemophilia

EQ5D5L, EuroQol 5-Dimension 5-Level questionnaire (version for adults); EQ5DY5L, EuroQol 5-Dimension Youth 5-Level questionnaire (version for children and adolescents); Haemo-Qol, Haemophilia quality-of-life; HEP-Test-Q, Haemophilia & Exercise Project-Test-Questionnaire; HJHS, Haemophilia Joint Health Score; MoMo-AFB, Motorik-Module Activity Questionnaire; VAS, Visual Analogue Scale.

The study will take place at the Haemophilia Treatment Centre at the Department of Paediatrics and Adolescent Medicine of the University Hospital Tübingen, a facility that provides specialised care in haemophilia management. Patients will be recruited from the outpatient clinic and all assessments will be carried out within the University Hospital. The setting allows access to technical infrastructure for video gait analysis recording, accelerometry devices as well as trained clinical staff for monitoring, intervention and follow-up.

### Participants and recruitment

Haemophilia care at the University Hospital Tübingen is provided through separate paediatric and adult divisions. Together, they manage approximately 30 patients with severe and 30 with moderate haemophilia, the majority of whom are children. The sample size for the feasibility pilot study is primarily guided by practical considerations.^30^ With a targeted recruitment rate of 40%, a sample size of 12 participants per group will be feasible. Methodological recommendations for feasibility studies suggest that samples of 12–30 participants per group are sufficient to assess feasibility outcomes such as recruitment rates, retention, data completeness and preliminary parameter estimates for future sample size calculations.^31^,^33^ Since the subgroups of severe and moderate haemophilia will be evaluated separately, the number of cases in each of these two groups is planned to be 12, resulting in a total of 48 participants (24 patients and 24 control subjects).

For each patient with haemophilia enrolled in this study, one healthy subject will be recruited to provide a normative reference dataset. The healthy subjects will be matched to the haemophilia patients based on age, gender, height and body mass. All patients of the Department of Paediatrics and Adolescent Medicine of the University Hospital Tübingen and healthy siblings from the age of 18 months will be able to participate in the study if they fulfil the inclusion criteria and none of the exclusion criteria applies (see table 1). Comparison with age-matched healthy controls will be essential due to the wide age range and heterogeneity of the study cohort. While most participants will be children, young adults will also be included to ensure a sufficient sample size in the moderate and severe haemophilia groups, given the rarity of the condition.

### Timeline

The timeline of the study protocol is summarised in figure 1. For every study participant, measurement data will be obtained two times in a 12-month period: in month 0 and in month 12. It is expected to include two patients and two healthy participants per month. Based on this estimate, a recruitment period of 1 year will be considered feasible. The total assessment time of the study will be 24 months.

**Figure 1 F1:**
[figure not shown]
The timing of the measurements and the process of the study.

Measurement data collection will take approximately 45 min per patient (video recording 15 min, HJHS 30 min), and the completion of questionnaires will take another 30 min. Subsequently, the wearable activity tracking device will be explained and handed out to the participants to be worn as a regular part of their daily routine for eight consecutive days. Measurement data of haemophilia patients will be collected during routine appointments in the coagulation clinic. Between the two measurement points, individual advice on activity, physiotherapy, muscle strengthening, joint protection and therapy will be provided to the haemophilia patients based on the results of the interim evaluation at month 6. Finally, the second measurement (month 12) will focus on the identification of any measurable changes in the collected data (gait analysis, HJHS, daily activity, questionnaires, etc). Thereafter, the results of all data collected and analysed over the 12-month study period will be communicated to each patient in a dedicated counselling session, including personalised recommendations for best joint health. Furthermore, the aggregated data analysis might provide general recommendations for haemophilia patients to maintain long-term joint health for all patients.

### Interventions and measurements

The interventions and measurements are summarised in table 2 and described in detail in the following sections.

### Assessment of feasibility

Throughout the pilot trial, the number of participants screened and those who are eligible and willing to participate are collected, as well as reasons for ineligibility or reported causes for refusal. To check for the practicability of the study interventions and measurements, the quality of data is reviewed during the entire study, especially the proportion of usable video gait recordings, proportion of missing data from accelerometry and questionnaire completion rates. If necessary, additional descriptions or assistance will be provided for the remaining study in order to improve data quality. Furthermore, the participants’ adherence to the video recordings, accelerometry and the questionnaires is acknowledged and the technical performance, sensitivity of measurements to detect change and unexpected problems during assessments and interventions are recorded. The retention rate and drop-out rate are documented to address acceptance.

### Gait analyses

The recording of standardised videos for the markerless gait analysis will take place in a separate room with a 9.5 m walkway. Walking trials will be captured simultaneously by a sagittal and a frontal camera (AXIS P1375 network camera, 1920×1080 pixels, 50 frames/s). The cameras will be mounted at a height of 50 cm. The frontal camera will be positioned along the walking direction to capture frontal or posterior views. The sagittal camera will be positioned perpendicular (90°) to the walking direction at a distance of 2.8 m from the centre of the walkway.^34^ To counteract distortions caused by the camera lenses at the boundaries of the video frames, only the middle section of the walking distance will be selected for further processing.

The measurements will be taken barefoot with shorts and tight T-shirts; consequently, the ankle, knee joints and hips will be clearly visible. The participants will receive standardised instructions and should walk at a self-selected speed. Three videos will be recorded for each participant, with each video capturing three walking directions (ie, back and forth along the walkway). The total recording will take approximately 15 min.

The cameras will capture participants fully, including their faces. The faces will be made unrecognisable using video editing software before further processing and pseudonymised storage of the videos. The qualitative, markerless gait analysis was evolved by the Children’s Hospital Tübingen and the Cluster of Excellence—Machine Learning for Science at the Eberhard Karls University Tübingen. The method is based on transfer learning with deep neural networks (figure 2) and uses open-source image recognition.

**Figure 2 F2:**
[figure not shown]
Qualitative gait analysis with standardised videos and evaluation using artificial intelligence.

To predict the key points automatically from the recorded sagittal plane videos, a pre-trained Mask R-CNN model is used and a TCFormer model pre-trained on the COCO Whole Body dataset is applied on the cropped images to detect the key points of the human.^35^ Twelve points of interest for 2D motion analysis (shoulders, hips, knees, ankles, heels and toes) are predicted, representing the joint centres and anatomical regions of interest for 2D gait analysis. To automate the identification of individual gait cycles in a given video, a machine learning model, specifically, a Gradient Boosting based classifier, is trained to predict the probability that a given frame is an initial contact event.^36^ The gait analysis is adapted to the special conditions of the analysed age group; proof of principle has been successfully completed in patients with juvenile idiopathic arthritis.^20^

The use of single trials or gait cycles from markerless systems can introduce additional variability in kinematic data.^37^ Therefore, the average of the biomechanical gait data from nine consecutive walking trials at self-selected speed will be calculated, and gait cycle time will be expressed in per cent. The prespecified clinical outcome parameters will be standard spatiotemporal parameters, including cadence (steps/min), stride length and gait speed (m/s) normalised to body height. Additionally, the average joint angle trajectories of the ankle, knee and hip joints in the sagittal plane will be determined.

### Haemophilia Joint Health Score

The HJHS is a clinical score that has been established and validated in haemophilia patients to evaluate joint health and joint changes (table 2). The HJHS assessed by physiotherapists is part of the routine follow-up consultations in all haemophilia patients, regardless of the presented pilot study to evaluate joint health and will take a maximum of 30 min.^13 14^

### Accelerometry

An accelerometer, Actigraph wGT3X-BT (ActiGraph, Pensacola, FL; CE marking EN60601-1-Medical Device General Safety Requirements), will be used to objectively assess the individual physical activity and rest periods of the participants on eight consecutive days during waking hours. The measuring device is equipped with Actigraph’s validated triaxial piezoelectric accelerometer and digital filter technology. Each accelerometer will be initialised with ActiLife 6 Lite version 13.6 (ActiGraph) according to a standardised procedure before being given to the patient.

The device will be issued to the participants to take home after the video recording (month 0 and month 12). The participants will be instructed to wear the device on their right hip with a strap. The Actigraph will be taken off for sleeping, bathing/showering, swimming and contact sports. To document no-wear time, the participants will be handed a standardised protocol. Recording will automatically end at midnight on the eighth day and the Actigraph will be subsequently sent back to analyse the recorded raw data (figure 3).

**Figure 3 F3:**
[figure not shown]
Quantitative motion analysis with accelerometry.

Raw data will be processed with ActiLife 6 full version 13.6, data will be integrated into 1 s epochs as recommended for children and adolescents.^38 39^ Activity intensities will be identified and categorised using validated vertical axis cut-points in unit counts per minute (cpm): sedentary behaviour (0–184 cpm), light (185–2424 cpm), moderate (2425–3268 cpm) and vigorous physical activity (≥3269 cpm).^40^

All data processing procedures will follow the recommendations by Migueles *et al* and the protocols of the motoric module of the nationwide, representative surveys on child and adolescent health.^39 41^ The datasets were considered valid based on international standards, requiring ≥8 hours of wear time on ≥4 weekdays and ≥1 weekend day.^42^ If there are fewer than 5 days with usable data, the participants will be asked to repeat the accelerometry. If still less than five valid days are provided, participants will be excluded from the analyses due to non-adherence.

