**Trial registration number:**

German Clinical Trials Registry (DRKS00032707).

STRENGTHS AND LIMITATIONS OF THIS STUDYProspective longitudinal monocentric pilot study evaluating the feasibility, practicability and acceptance of quantitative and qualitative motion analysis in patients with haemophilia.Multimodal assessment combining markerless video-gait analysis, accelerometry, physical examination and patient-reported questionnaires.Innovative artificial intelligence-based assessment of video-gait analysis to test clinical application for the first time.Primary outcomes include recruitment rates, participant adherence and data quality to inform the design of a future multicentre study.Limitations include small sample size, single-centre design, high participant burden, potential bias in self-reports, uncertain adherence to accelerometry, and limited statistical power and interpretability due to heterogeneity.

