### Aim and objective

The aim of this pilot study is to test the feasibility, practicability and acceptance of the procedures for a quantitative and qualitative motion analysis for early detection of joint damage in haemophilia patients and to identify necessary adjustments for a larger, more comprehensive study.

To assess the feasibility of the study protocol, recruitment rates will be estimated and reasons for ineligibility or refusal will be analysed. The practicability and appropriateness of the study procedures and methods will be evaluated based on data on the proportion of usable video gait recordings, participants’ adherence to accelerometry, proportion of missing data, questionnaire completion rate, sensitivity of measurements to detect changes and unexpected problems during assessments. The acceptance of the study will be determined by evaluating the retention and the dropout rate.

This clinical trial has feasibility as its only primary objective. All clinical outcomes are considered exploratory. The main exploratory outcomes are the detection of early movement changes through markerless video gait analysis and the evaluation of joint health using the HJHS. Secondary clinical outcomes are anthropometric indices, clinical parameters, activity metrics from accelerometry and PROMs from questionnaires on daily activity and quality of life.

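### The accelerometry repeat and exclusion triggers count five days, but the validity rule also requires a weekday/weekend mix, so some invalid recordings trigger neither step

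*Protocol article*

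**What the plan says.** The Accelerometry section of the protocol article has the hip-worn device used "on eight consecutive days during waking hours", at month 0 and again at month 12. Three consecutive sentences then govern what happens to the recording:

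- Validity: "requiring ≥8 hours of wear time on ≥4 weekdays and ≥1 weekend day".
- Repeat: "If there are fewer than 5 days with usable data, the participants will be asked to repeat the accelerometry".
- Exclusion: "If still less than five valid days are provided, participants will be excluded from the analyses due to non-adherence".

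Accelerometry activity is a secondary clinical outcome (Table 1), but adherence to wearing the device has a higher standing. Under Aim and objective the article says "This clinical trial has feasibility as its only primary objective". The strengths and limitations box says "Primary outcomes include recruitment rates, participant adherence and data quality". Table 2 lists, under practicability, "Proportion of usable video gait recordings, participant adherence to accelerometry, proportion of missing data". Statistical methods says that adherence and missing data will be summarised.

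**The concern.** The first rule sets a composition: enough weekdays and at least one weekend day. The second and third set only a number of days. A participant can therefore have a dataset that is not valid by the first rule and still not be asked to repeat or be excluded.

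Two things are at stake.

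- **Activity estimates.** Followed as written, the plan either loses data that a repeat week might have recovered, or lets weeks without the required mix into the summaries. A week with no weekend day says nothing about weekend activity.
- **Adherence.** The exclusion sentence is the only place where the article classes anyone as non-adherent, and it does so by the count. Two analysts could class the same child differently: adherent because five days were worn, or not adherent because the dataset is invalid.

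**Working it through.** **Inputs.** From the Accelerometry section: an eight-day recording; a valid dataset needs at least 8 hours on at least 4 weekdays and at least 1 weekend day; the trigger for repeat and exclusion is fewer than 5 days. From Participants and recruitment: 48 participants. I take a usable or valid day to be one with at least 8 hours of wear. The start day is not given. Any eight consecutive days starting Monday to Friday hold 6 weekdays and 2 weekend days (6+2); a Saturday or Sunday start gives 5 and 3 (5+3).

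**Step 1: the plan's own figure.** The smallest dataset that meets the validity rule has 4 + 1 = 5 days, so the five-day threshold reproduces as a minimum count. No dataset with fewer than five days can be valid. The mismatch runs in one direction only: five days are necessary but not sufficient.

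**Step 2: count the patterns.** Write w for valid weekdays and e for valid weekend days. In the 6+2 window the number of day patterns with a given (w, e) is C(6,w) × C(2,e). Those with w + e ≥ 5 are:

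| (w, e) | Patterns | Meets validity rule? |
|---|---|---|
| (3,2) | 20 | no |
| (4,1) | 30 | yes |
| (4,2) | 15 | yes |
| (5,0) | 6 | no |
| (5,1) | 12 | yes |
| (5,2) | 6 | yes |
| (6,0) | 1 | no |
| (6,1) | 2 | yes |
| (6,2) | 1 | yes |

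The total is 93, and 20 + 6 + 1 = 27 fail (27/93 = 29%). In the 5+3 window the total is again 93, and the failing patterns are (2,3), (3,2), (3,3) and (5,0): 10 + 30 + 10 + 1 = 51 (51/93 = 55%). These are counts of patterns, not probabilities.

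**Step 3: how often it might happen.** This needs daily wear probabilities, which the article does not give, so what follows rests on assumptions. Let p be the chance that a weekday is valid and q the chance that a weekend day is valid, with days independent. For the 6+2 window:

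gap = 20·p³(1−p)³·q² + [6·p⁵(1−p) + p⁶]·(1−q)²

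| p | q | (3,2) | (5,0) | (6,0) | Gap | Of 48 recordings |
|---|---|---|---|---|---|---|
| 0.9 | 0.9 | 0.0118 | 0.0035 | 0.0053 | 2.1% | 1.0 |
| 0.8 | 0.8 | 0.0524 | 0.0157 | 0.0105 | 7.9% | 3.8 |
| 0.6 | 0.6 | 0.0995 | 0.0299 | 0.0075 | 13.7% | 6.6 |
| 0.90 | 0.75 | 0.0082 | 0.0221 | 0.0332 | 6.4% | 3.1 |
| 0.90 | 0.40 | 0.0023 | 0.1275 | 0.1913 | 32.1% | 15.4 |

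With equal probabilities from 0.5 to 0.9 the gap runs from about 2% to 14%. With p from 0.70 to 0.90 and q from 0.40 to 0.75, the smallest and largest values over the whole grid are the last two rows, 6.4% and 32.1%. In the 5+3 window, equal probabilities of 0.5, 0.6, 0.7, 0.8 and 0.9 give 19.9%, 27.9%, 29.2%, 21.2% and 7.7%. The last column of the table supposes that all 48 participants return a recording in that assessment round.

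**The case against.** The best defence is that the three sentences stand together and 4 + 1 = 5, so five valid days may be shorthand for the rule just stated. On that reading the triggers and the validity rule agree. Even on the literal reading, a 5+0 dataset remains invalid by the first sentence, so a careful team would keep it out of the activity summaries. Both points are fair, and they limit the harm. They do not remove the gap: the text nowhere equates the count with the composition, and on the literal reading an invalid dataset still prompts no repeat and has no stated adherence status. Nor is this detail that a condensed article may leave to a fuller document, because the article itself states all three rules and they do not match.

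Two stronger readings are tempting, and the article does not support either.

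- **Loss of other data.** A reader might infer that excluding participants from the analyses also removes their gait, HJHS and questionnaire data. The sentence sits in the Accelerometry section, straight after the accelerometry validity rule, and nothing elsewhere makes the other analyses conditional on accelerometry. Statistical methods also plans to examine patterns of missing data, which presupposes that participants with missing components are kept. Exclusion from the accelerometry analyses is the likely intent; its scope is merely unstated.
- **Inflated adherence.** A reader might infer that non-adherers leave the adherence denominator, or that success after a repeat is counted in a way that biases the rate upward. No section says that non-adherers leave the denominator, and the exclusion sentence identifies them as non-adherent. If the repeat is part of the procedure under test, adherence after the repeat is a legitimate feasibility figure. Putting first-wear adherence first would be a preference, not a correction.

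It also stands that accelerometry activity is a secondary, exploratory outcome, that no hypothesis is tested, and that the sample size of 48 is unaffected.

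**Conclusion.** The mismatch is real and rests on counting alone: 27 of 93 patterns with at least five days (6+2 window), or 51 of 93 (5+3 window), are invalid but trigger neither a repeat nor an exclusion. Their place in the activity estimates and in the adherence measure is undefined.

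How many participants this would affect cannot be settled from the article. In the 6+2 window the assumed ranges give about 1 to 7 of 48 recordings per round if weekdays and weekend days are worn equally well, and about 3 to 15 of 48 if weekend wear is poorer. Real days within one participant are unlikely to be independent, so these figures show the order of size only.

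Severity is moderate. The outcome is secondary, but the same rule feeds accelerometry adherence, one of the practicability measures under the primary feasibility objective. The finding does not extend to a biased adherence rate or to the loss of gait, HJHS or questionnaire data.

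**What to change.** - **Main change.** Use one criterion throughout. Ask for a repeat when the dataset does not have at least 8 hours of wear on each of at least 4 weekdays and at least 1 weekend day, and apply the same criterion after the repeat to decide on exclusion.
- **Clarification.** Say that the exclusion applies only to activity outcomes derived from accelerometry, and that the participant still counts as non-adherent in the adherence rate.

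The change is to wording only. It costs a few more repeat requests and possibly a slightly lower adherence figure. It should be settled before recordings are classified.
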